### Objectives

#### Overview

This study aims to identify ITE and their prevalence using device-specific checklists based on manufacturers’ guidelines for 13 inhaler types across all lung conditions and to correlate these errors with possible determinants of poor technique. It also aims to assess the error frequency at each step in the device-specific questionnaires, compare error rates among device types, and determine which of these errors are deemed *critical* or *noncritical*.

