#### Secondary Objectives

The secondary objectives are as follows:

To assess whether the frequency of ITE are associated with participant demographics, respiratory diagnosis, and comorbidities; disease control as measured by questionnaires, such as Asthma Control Questionnaire (ACQ) for asthma and COPD Assessment Tool (CAT) score for COPD, and participant clinical characteristics including exacerbation frequency within the past 12 months; length of time a participant has been using the observed inhaler, along with previous device-specific inhaler technique training (if and when previous training has taken place and given by whom); and levels of behavioral and adherence risk profile as measured by the social, psychographic, usage, and rational (SPUR) profiling tool (Observia).To assess the user error frequency at each step in the device-specific guidelines.To compare user error rates among device types.

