#### Exploratory Objectives

The exploratory objectives are as follows:

To categorize ITE as *critical* or *noncritical* and prioritize the importance of these errors by conducting a further study outside the remit of this protocol and involves a Delphi consensus process. Owing to ongoing debate and variations in the definitions of critical and noncritical errors, final definitions will be based on the outcomes of the Delphi consensus process. The information from the Delphi process, along with the data from this prevalence study, will be collated to determine which ITE will be included in a subsequent study, in which a scoring system to quantify ITE will be developed.To correlate severity of disease with ITE if a disease-specific tool is available. The GINA step will be used for asthma and GOLD stage for COPD with spirometry, whereas forced expiratory volume in 1 second (FEV_1_), forced vital capacity (FVC), and FEV_1_/FVC ratio measurements will be used if spirometry is performed as part of standard care.

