### Eligibility Criteria

Participants will be drawn from a range of clinical conditions affecting adults that use an inhaler device. The inclusion and exclusion criteria are presented in Textbox 1.

Inclusion and exclusion criteria.

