#### Disease Severity

If possible, disease severity will be categorized. For participants with asthma, it will be step 1-5, as per the GINA guidelines. In patients with COPD, this will be categorized as A-D using the GOLD guidelines with the severity of airflow limitation based on current or last available spirometry results within the last 12 months combined with their CAT score and exacerbation history. For participants with respiratory conditions other than asthma and COPD, the number of exacerbations in the last 12 months and lung function, if available, will be used to determine disease severity.

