#### Secondary Analysis

The secondary analysis will compare the error rates for different background measures. In all cases, the choice of test will depend on whether the number of events is normally distributed. Parametric tests will be used in the first instance, unless there is evidence of nonnormality as assessed using a Shapiro–Wilk test, in which case a nonparametric alternative will be used.

CAT scores will be categorized for the purposes of analysis, with scores of 0-10, 11-20, 21-30, and 31-40 representing mild, moderate, severe, and very severe clinical impact, respectively. One-way ANOVA or Kruskal–Wallis tests will be used to assess whether there is any significant difference in the number of errors among CAT categories.

Exacerbation frequency within the last 12 months will similarly be categorized for the purposes of analysis, with the categories of xx-xx and yy-yy used. One-way ANOVA or Kruskal–Wallis tests will be used to assess whether there is any significant difference in the number of errors between CAT categories.

The association between the number of errors and continuous measures of FEV_1_, FVC, and FEV_1_/FVC ratio will be assessed using bivariate correlation. If the multivariate normality assumptions of the Pearson correlation are not met, logged values of the number of errors will be used to correct for this. If the logged values are still nonnormal, Spearman rank correlation coefficients will be used instead.

The severity of asthma will be measured using the GINA stepwise treatment guide. This measure will be categorized according to the GINA level, and comparisons between the number of errors will be assessed using a one-way ANOVA or Kruskal–Wallis test if the parametric assumptions of the former test are not met.

The severity of COPD will be categorized according to the GOLD stage, which is supplied in the form of categories. One-way ANOVA or Kruskal–Wallis tests will be used to assess whether there is any significant difference in the number of errors among GOLD levels.

Previous device training will be categorized on the basis of whether patients had received previous training. This will be classified as a binary yes or no contrast. Differences in the number of errors will be tested using an unpaired *t* test, or in the event of nonnormality, a Mann–Whitney *U* test.

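### The lung-function correlations take no account of diagnosis, so a difference between diseases can look like, hide or reverse a severity gradient

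*Protocol article*

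**What the plan says.** All references are to the protocol article.

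- **Method.** Under Secondary Analysis, the link between number of errors and FEV1, FVC and the FEV1/FVC "ratio will be assessed using bivariate correlation". The fallbacks concern distribution only: log the error count, and then "If the logged values are still nonnormal, Spearman rank correlation coefficients will be used instead".
- **Population.** The Objectives overview describes a study "for 13 inhaler types across all lung conditions". Eligibility Criteria adds: "Participants will be drawn from a range of clinical conditions affecting adults that use an inhaler device".
- **Purpose.** The Exploratory Objectives include "To correlate severity of disease with ITE if a disease-specific tool is available", and the same item brings in FEV1, FVC and their ratio where spirometry is done in standard care.
- **Other diagnoses.** Under Disease Severity, for conditions other than asthma and COPD, exacerbation count and "lung function, if available, will be used to determine disease severity". These participants can therefore enter the correlation.
- **Diagnosis and errors.** The Secondary Objectives ask whether errors are "associated with participant demographics, respiratory diagnosis, and comorbidities".
- **Contrast.** The neighbouring severity tests are each tied to one disease. For asthma, "The severity of asthma will be measured using the GINA stepwise treatment guide"; GOLD is used for COPD.

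**The concern.** A bivariate correlation has two variables, so it has no place for diagnosis. No subset is named either. Carried out as written, it is computed over everyone with spirometry, whatever the diagnosis.

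The severity question is whether, among people with a given disease, worse lung function goes with more errors. FEV1 and FEV1/FVC can be expected to differ between asthma, COPD and other conditions because the diseases differ. Error counts may differ by diagnosis too, and the study sets out to test that. If both differ, the pooled coefficient picks up the contrast between diseases. A gradient may then be reported that exists inside no disease, or a real one may be lost or change sign.

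Confounding by device, and the choice between litres and percent predicted, are separate matters. Handling them would not remove this one.

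**Working it through.** **Inputs from the protocol.** The minimum sample is 13 × 50 = 650, as stated; that figure is not in dispute. Spirometry is recorded only where routine care provides it, or from the past 12 months, so the n for this analysis is unknown and probably well below 650. No mean or SD of lung function or errors by diagnosis is given, and no power calculation was done. Everything below is therefore assumed, including a two-sided 5% test.

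**Step 1: formula.** Take two diagnoses with proportions p and 1−p. Let d and e be the gaps between them in lung function and in errors, in within-diagnosis SDs, and let ρ be the correlation inside each diagnosis. The pooled correlation is

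r = [ρ + p(1−p)de] / √{[1 + p(1−p)d²][1 + p(1−p)e²]}.

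The chance that the test rejects follows from Fisher's z, with mean atanh(r)·√(n−3).

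**Step 2: no association within disease (ρ = 0, p = 0.5).**

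| d | e | \|r\| | Rejection at n=200 |
|---|---|---|---|
| 0 | any | 0 | 5% |
| any | 0 | 0 | 5% |
| 0.5 | 0.3 | 0.0375/√(1.0625 × 1.0225) = 0.036 | 8% |
| 1.0 | 0.4 | 0.10/√(1.25 × 1.04) = 0.088 | 24% |
| 1.5 | 0.4 | 0.15/√(1.5625 × 1.04) = 0.118 | 38% |
| 1.8 | 0.52 | 0.232/√(1.81 × 1.067) = 0.167 | 66% |

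The last row takes FEV1/FVC means of 0.72 and 0.54 with SD 0.10, so d = 0.18/0.10 = 1.8. Poisson error means of 2.0 and 2.8 give e = 0.8/√2.4 = 0.52.

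**Step 3: simulation with Spearman's coefficient.** With the last row's FEV1/FVC values and error means of 2.0 versus 2.3 to 2.8, pooled r is −0.07 to −0.17. Rejection is 16% to 69% at n=200. After diagnosis means are removed from the ranks, it is 4% to 6%.

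A three-diagnosis version used shares of 45/45/10%, FEV1/FVC means 0.72/0.52/0.70 and error means 2.0/2.5/2.2. It gives r = −0.11 and rejection of 33%, 49% and 77% at n = 200, 325 and 650. With equal error means it stays at about 5%. Combining within-diagnosis coefficients gives 4.6% to 5.8% in every scenario.

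**Step 4: masking and reversal.** Give each disease a true gradient: the error mean is multiplied by exp(−0.12) per within-disease SD of FEV1/FVC. Set asthma errors at 2.5 and COPD at 2.0. Pooled r is about −0.01 and the pooled test rejects in about 5% of studies. With diagnosis removed it rejects in about 65% (n=200) and 92% (n=400).

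Reversal follows from the Step 1 formula. Let the disease with lower lung function make fewer errors, with ρ = −0.10, d = 1.8 and e = 0.5. Then r = (−0.10 + 0.225)/√(1.81 × 1.0625) = +0.09, opposite in sign to the gradient inside each disease.

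**The case against.** - **Pooling is inferred.** The text never says that diagnoses are combined, and an unseen SAP might stratify. The first part is true. But a two-variable method is stated, its fallbacks are spelled out, and the tests beside it are each limited to a disease while this one is not. That is a method fixed in the text, not a detail left open.
- **Rejecting is not an error.** When both gaps exist, the overall correlation really is non-zero, so the test of that null is right to reject. This stands, and the rates above should not be called false-positive rates of the bivariate test. The fault lies in reading the coefficient as evidence on severity, which is the use the Exploratory Objectives give these measures.
- **Severity is already examined by disease.** GINA and GOLD give disease-specific results. This stands and limits the harm, but it does not make the lung-function coefficient interpretable.
- **The size depends on chosen inputs.** This stands. Only FEV1/FVC was simulated, and its 1.8 SD gap is large. With gaps of 1.0 and 0.4 SD and n=100, rejection is about 14%; with 0.5 and 0.3 SD it is about 6%.
- **Other secondary tests are unadjusted too.** True, but here the covariate is one the protocol itself names, and the target question is specific to a disease.

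**Conclusion.** The point holds as a conditional one. As written, the lung-function correlations cannot separate a severity gradient within diseases from differences between them.

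The distortion needs both lung function and error count to differ by diagnosis. Across the assumed gaps examined in Step 2, with no association within disease, it runs from nothing (5% rejection) through |r| of about 0.04 to about 0.17 (66% by formula, 69% by simulation, at n=200).

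A reader might infer three stronger claims that the documents do not support:

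- That a disease difference will appear as a severity effect. The protocol gives no figure for either gap and lists diagnosis only as a factor to be tested.
- That a high rejection rate is to be expected. The upper figures rest on one assumed FEV1/FVC gap and an assumed n.
- That the severity objective as a whole, or the primary comparison of devices, is compromised. The primary, GINA and GOLD analyses are unaffected, and this analysis is secondary or exploratory in the spirometry subset.

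**What to change.** In Secondary Analysis, replace the plain bivariate correlation with a partial Spearman correlation of error count with each of FEV1, FVC and FEV1/FVC, adjusted for diagnosis as asthma, COPD or other. Report the within-diagnosis coefficients beside it. Include other diagnoses where numbers allow: restricting them to description would conflict with the Disease Severity section, which relies on lung function for those participants. If an unadjusted coefficient is also shown, label it descriptive and do not interpret it as evidence on severity.

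The change is one of wording, since diagnosis is already recorded on the case report form. It costs one or two degrees of freedom for the adjusted estimate and less precise coefficients within each diagnosis.

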#### Procedure for Missing, Unused, or Spurious Data

There are no plans for multiple imputation or other corrections for missing data.

### Ethical Considerations

#### Statement of Compliance

All staff working on this study will hold evidence of good clinical practice training before undertaking any responsibilities, and all staff working within the research study team are also part of the respiratory clinical care team. Written informed consent will be obtained from all participants after an adequate explanation of the aims, methods, and anticipated benefit of the study using the participant information sheet. A signed copy of the consent form will be given to the participant, and copies will be filed in the study master file and the participants’ medical notes.

Participants’ anonymity will be maintained throughout by identification on a password-protected electronic database and CRFs only by initials and participant ID number. All documents will be stored securely and only accessible by study staff and authorized personnel; the study will comply with the Data Protection Act.

#### Potential Benefits or Risks of Study Participation

By participating in this study, participants who are observed making errors with their inhaler technique will have these errors highlighted and will be reeducated. This is a beneficial outcome for participants’ self-care and management and ensures that they maximize drug delivery from their inhaler.

This study analyzes a wide variety of inhaler devices and will help provide a clear picture of the inhalers that are associated with the most errors. Understanding this information is important in the context of managing lung conditions, from treating patients in primary care through to feeding this information back to device manufacturers.

Any risks to the participants have been carefully considered. Participants found unable to use the inhaler device they have been prescribed will have an alternative device issued if possible, or a letter will be written to their GP with the recommended new device as per clinical practice.

#### Other Ethical Considerations

The study was approved by the Hampshire A Research Ethics Committee (REC; REC reference 19/SC/0286) in August 2019. They reviewed and approved the protocol and all relevant study materials. Any changes to the protocol or relevant study documents will be approved by the sponsor. If an amendment is made that requires REC approval, as defined by REC as a substantial amendment, the changes will not be instituted until the amendment has been reviewed and received approval or favorable opinion from the REC and research and development departments. A protocol amendment intended to eliminate an apparent immediate hazard to participants may be implemented immediately, provided that the REC is notified as soon as possible and that an approval is requested. Minor amendments as defined by REC as a nonsubstantial amendment may be implemented immediately and the REC will be informed. All participants will have adequate time to consider participation in the study, as per the Good Clinical Practice guidelines.

Patients who are already enrolled in other research trials will be invited and allowed to participate in the study if they wish. This was discussed with our Patient Public Involvement representatives who felt that these patients should have the opportunity to participate in this study and should not be excluded.

### Patient Public Involvement Process

Patient involvement in this study has been sought from patients with first-hand experience of living with chronic respiratory disease. Through face-to-face meetings, e-mail, and telephone contact, we have discussed the concept, impact, and details of the study with our respiratory patient representatives from local British Lung Foundation groups. These people have lived with respiratory conditions and have been involved in previous research studies. They contributed to developing the key questions and setting our study objectives, ensuring that we answer the questions that are relevant to people suffering from airway diseases. Assistance was also sought with participant recruitment design and the implementation of the study within a standard clinical visit to minimize delays for patients who agreed to participate in the study. They also helped design the participant information sheet and coauthored the lay summary.

## Results

Recruitment into the study has already commenced, with the study scheduled to be closed to recruitment by December 2021. It is anticipated that the results will be available by late 2022.

## Discussion

The SCORES (Study to Investigate the Prevalence of Device-Specific Errors in Inhaler Technique in Adults With Airway Disease) study will provide valuable information on the frequency of ITE. These errors will enhance health care professionals’ knowledge on this important subject, and by correcting their inhaler technique, participants will benefit from the study.

## Abbreviations

ACQ: Asthma Control Questionnaire
ANOVA: analysis of variance
CAT: Chronic Obstructive Pulmonary Disease Assessment Test
COPD: chronic obstructive pulmonary disease
CRF: case report form
FEV_1_: forced expiratory volume in 1 second
FVC: forced vital capacity
GINA: Global Initiative for Asthma
GOLD: Global Initiative for Chronic Obstructive Lung Disease
GP: general practitioner
ITE: inhaler technique errors
NHS: National Health Service
REC: Research Ethics Committee
SCORES: Study to Investigate the Prevalence of Device-Specific Errors in Inhaler Technique in Adults With Airway Disease
SPUR: social, psychographic, usage, and rational
